## 8.2 Analytical plan and sample size/power calculations

Statistical analysis will be undertaken using Stata 10 (Stata Corp., College Station, TX, USA). The prevalence of malaria infection will be based on the thin and thick blood smear readings. This procedure will enable estimation of parasite density, differentiation of Plasmodium species and identification of gametocytes. The proportion of children infected with single and multiple parasite species and the mean intensity of infection/parasite density will be calculated. Differences in proportions by age, sex and transmission setting will be assessed by logistic regression and differences in means using a Student t-test (for parametric data) and a Mann-Whitney test (for non-parametric data). Prevalence of infection and anemia, and coverage rates will be presented as frequencies with appropriate 95% binomial confidence intervals. The report and other related documents will be extensively disseminated to stakeholders. Avenues for dissemination will include publications, working papers, and atlases.

Infection. The primary metric used to measure infection for both the gold standard method (community surveys) and streamlined method (school surveys) will be the parasite rate (PR), defined as the number of positive blood smears divided by the number of smears examined. For the gold standard method, PR will be measured using the cross-sectional surveys of an estimated 300 children (200 households x 1.5 children per household) aged 6-14 years from the community surveys. For the streamlined method, PR will be estimated using cross-sectional surveys of 300 children (3 schools x 100 children per school) aged 6-14 years from the primary school surveys.

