We will test the hypothesis that estimates of PR will be similar using the two methodologies. Point estimates of PR will be calculated for each biannual survey and compared using the McNemar’s test of paired proportions. Assuming that we will have a sample size of 300 children per survey for each methodology, we will have 80% power (one-sided significance level of 0.05) to reject the alternative hypothesis that there is a difference in estimates of PR assuming that the absolute difference in PR is no greater than 10% across a range of PRs in the community surveys of 20-80%. Whether or not these analyses show any evidence of significant differences between the methods, we will explore whether there is any systematic bias in the estimate of the streamlined method compared to the gold standard method (e.g. the streamlined method consistently over- or underestimates PR). Ecological logistic regression models will be used to predict the result of the gold standard method using data from the streamlined method, allowing adjustment for bias. Final models will then be prospectively validated in independent test sets to insure their accuracy.

Mortality. The primary metric for malaria mortality will be the relative change in absolute measures of malaria mortality. For the gold standard method, the measure of malaria morality will be the number of malaria-associated deaths in children under 5 years of age per 1,000 live births. Data on malaria mortality using the gold standard method will come from the biannual community surveys and verbal autopsy. For the streamlined method, the measure of malaria morality will be the number of malaria-associated deaths in children under 5 years of age captured by our inpatient surveillance system (described in another protocol).

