We will test the hypothesis that relative changes in malaria mortality will be similar using the two methodologies. Point estimates of relative mortality from one year to the next will be calculated and compared, by calculating the variance of the streamlined method using the delta method and the variance of the gold standard method using a bootstrap test. Assuming that we will have a sample size of 800 children per year from the community surveys with baseline mortality rates of 6.5, 12.9, and 19.4 per 1000 (based on 2006 Uganda DHS survey and assuming malaria-attributable mortality of 20%, 40%, and 60%), and baseline number of malaria-associated deaths from our inpatient surveillance of 12, 60, and 84 (based on preliminary inpatient surveillance data) for low, medium, and high transmission sites respectively, we will have 80% power (one-sided significance level of 0.05) to reject the alternative hypothesis that there is an absolute difference in estimates of relative mortality of 1.30, 0.50 and 0.41 for low, medium, and high transmission sites, respectively. Whether or not these analyses show any evidence of significant differences between the methods, we will explore whether there is any systematic bias in the estimate of the streamlined method compared to the gold standard method (e.g. the streamlined method consistently over- or underestimates relative mortality). Log-linear regression models will be used to predict the result of the gold standard method using data from the streamlined method, allowing adjustment for bias.

Immunology. The age-dependent SCR will be determined for each study area at each time-point and related to the concurrent parasite prevalence by RDT, microscopy and PCR and anemia prevalence.

Evidence for a change in transmission intensity will be assessed by fitting more than one force of infection to age-dependent antibody prevalence data. Antibody prevalence and density in school children will be related to the concurrent parasite prevalence by RDT, microscopy and PCR and anemia prevalence.

Decision on the optimal methods for surveillance. If any of the streamlined methods described above do not approximate the corresponding gold standard methods and attempts at correcting systematic bias are not reliable (e.g. unable to consistently predict estimates using the gold standard method) then we will conclude that the streamlined method is not a reasonable substitute for the gold standard method.

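### School and community parasite rates are to be compared with a paired test although the two samples contain no pairs, and the test is not tied to the protocol's own 10-point limit

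*Protocol*

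**What the plan says.** The Infection paragraphs of Protocol section 8.2 set out the comparison that serves specific objective 2 (section 3.2). The aim is "We will test the hypothesis that estimates of PR will be similar using the two methodologies". For each biannual survey the point estimates are to be "compared using the McNemar’s test of paired proportions".

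The community estimate comes from "an estimated 300 children (200 households x 1.5 children per household) aged 6-14 years from the community surveys". For the schools, "PR will be estimated using cross-sectional surveys of 300 children (3 schools x 100 children per school) aged 6-14 years".

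The power statement begins "Assuming that we will have a sample size of 300 children per survey for each methodology" and claims "80% power (one-sided significance level of 0.05) to reject the alternative hypothesis that there is a difference in estimates of PR", on the assumption that "the absolute difference in PR is no greater than 10% across a range of PRs in the community surveys of 20-80" per cent.

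The sampling is described elsewhere. Section 5.1.1 draws households at random from an enumerated list. Sections 6.1 and 6.3 draw three schools at random from a list of primary schools and then pupils from the school registers. Both draws are renewed for every survey. No section describes matching or linking children between the two surveys.

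The last paragraph of section 8.2 gives the decision rule, which opens "If any of the streamlined methods described above do not approximate the corresponding gold standard methods" and also requires that attempts to correct bias have proved unreliable. It puts no number on how close is close enough.

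**The concern.** McNemar's test applies when each unit has been classified by both methods. It uses only the units on which the two classifications disagree. Here one group of children is seen at home and a separately drawn group is seen at school, so the table of agreements and disagreements cannot be built. The community figure of 300 is itself only an estimate, so the two groups need not even be the same size.

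Pairing by site and survey does not help. McNemar's test needs a yes/no outcome from each member of a pair, and a PR estimate is not one.

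There is a second mismatch. The hypothesis is that the methods agree, and the power sentence is worded like an equivalence claim with a 10-point limit. The only test named is a test of difference, and nothing connects its result to that limit. Objective 2, and part of the decision on whether school surveys can stand in for community surveys, rest on this comparison.

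**Working it through.** **Inputs, all from section 8.2:** 300 children per method, one-sided 0.05, 80% power, 10 points absolute, community PR 20–80%. No within-pair correlation, discordant proportion or intracluster correlation (ICC) is given.

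**1. Reproducing the stated 80%.**
- Independent samples, one-sided difference test, 50% against 60%: SE under no difference = √(2×0.55×0.45/300) = 0.0406; SE under the alternative = √((0.25+0.24)/300) = 0.0404. Power = Φ[(0.10 − 1.645×0.0406)/0.0404] = Φ(0.82) = 79.4%.
- Independent samples, one-sided 10-point limit, true difference 0, PR 50%: SE = √(2×0.25/300) = 0.0408. Power = Φ(0.10/0.0408 − 1.645) = Φ(0.805) = 78.9%.
- McNemar with 300 pairs, 50% against 60%: 79.2% if the within-pair correlation is zero, but 86.4%, 93.6% and 98.7% at correlations of 0.2, 0.4 and 0.6.

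So the stated power is about right at its worst point for two unpaired, unclustered samples. It agrees with a paired calculation only if the pairing carries no information.

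**2. What McNemar's test returns without real pairs.** Take 150/300 positive in one survey and 127/300 in the other (illustrative counts). The statistic is z = (b − c)/√(b + c), where b and c are the two kinds of discordant pair. The gap b − c is fixed at 23, but b + c depends on the ordering of the children.

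| Pairing | b, c | z | two-sided p |
|---|---|---|---|
| Positives matched to positives | 23, 0 | 23/√23 = 4.80 | 0.0000016 |
| Positives matched to negatives | 150, 127 | 23/√277 = 1.38 | 0.17 |
| 10,000 random pairings | varies | varies | about 0.03 to 0.09 |

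The independent-samples test has one answer: difference 0.0767, pooled proportion 277/600 = 0.462, SE = √(0.462×0.538×2/300) = 0.0407, z = 1.88, p = 0.060.

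**3. Difference test against a similarity hypothesis.** Suppose the true gap is a full 10 points. Even a valid two-sided 5% difference test with 300 per method, unclustered, has power 80.9% at 20% against 30% and 69.3% at 50% against 60%. It would be non-significant in about 19% and 31% of surveys respectively. Non-significance is therefore weak evidence of agreement within 10 points.

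**4. Power of a test that matches the hypothesis.** Two one-sided 0.05 tests against ±10 points, true difference 0, no clustering: power = 2Φ(0.10/SE − 1.645) − 1, with SE = √(2p(1−p)/300).

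| PR | SE | Power |
|---|---|---|
| 20% or 80% | 0.0327 | 84.4% |
| 30% or 70% | 0.0374 | 69.6% |
| 40% or 60% | 0.0400 | 60.8% |
| 50% | 0.0408 | 57.9% |

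For 80% power at PR 50%: n = 2×0.25×(1.645+1.282)²/0.10² ≈ 429 per method.

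**5. Effect of school clustering (ICC assumed).** With 100 pupils per school the school design effect is 1 + 99×ICC. Leaving household clustering out, SE = √[p(1−p)/300 × (1 + design effect)]. At PR 50%, an ICC of 0.01 (design effect 1.99) gives power 28%, 0.02 (2.98) gives 7%, and 0.05 (5.95) gives 0%. At PR 20% the figures are 61%, 40% and 0%.

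**The case against.** Four points can be made for the plan.

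First, the power sentence is worded in equivalence style, with a limit and a one-sided level. A reader might infer that the protocol commits itself to treating a non-significant McNemar result as proof of similarity. It nowhere says so. What stands is narrower: with this test and no rule using the limit, a non-significant result is the only outcome that could be offered in support of the hypothesis. That is an inference.

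Second, a reader might infer that this p-value decides whether school surveys replace community surveys. It does not. Section 8.2 explores systematic bias whatever the test shows, fits regression models to predict the community result, validates them prospectively, and rejects the school method only if it fails to approximate the community method and correction is also unreliable. This softens the consequence, but the comparison still has no valid result.

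Third, a reader might hold that every site and survey must pass, or measure the defect by the false-positive rate of an unclustered two-sample test. The protocol contains no rule that all comparisons succeed and does not propose that test. Ignored clustering is a separate matter.

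Fourth, a child could by chance fall into both surveys. Nothing identifies such a child, so this creates no usable pairs. A statistical analysis plan, not shown here, might correct the test, but the protocol does not leave the choice open: it names one.

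**Conclusion.** The point holds on the protocol's own text. A paired test is specified for two separately drawn, unlinked samples, and its p-value is arbitrary: 0.0000016 to 0.17 on the same illustrative counts. The named test also does not address the stated hypothesis, because the 10-point limit appears only in the power sentence.

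The sample size and the 80% are not wrong for an unclustered, one-sided, independent-samples calculation. They cease to apply once the analysis matches a two-sided similarity claim. Section 8.2 is itself concerned with both over- and underestimation, so two-sided limits are needed. The 58% to 84% power assumes no true difference and no clustering. The lower figures rest on assumed ICCs, since the protocol gives none.

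**What to change.** In section 8.2, replace McNemar's test with the difference in PR, school minus community, for two independent samples. Use a variance that allows for clustering by school and household, for example a mixed model with random effects for both. With three schools per site and survey, the school component will be poorly estimated from any single survey, so it is better estimated from all surveys together.

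State the rule: similarity is concluded only if the 90% confidence interval for the difference lies wholly within ±10 points. Report it for each site and survey. A pooled difference, stratified by site and survey, may be added but should not replace the site-specific results, because opposite biases at different sites could cancel in it.

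Restate the power for this analysis, with an explicit ICC or a range of ICCs. Tie the decision paragraph at the end of section 8.2 to the same limit, so that approximating the community method has a numerical meaning.

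The cost is a little more analysis and a less favourable stated power. No extra data are needed.

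### The 80% power for showing similar parasite rates is a one-directional figure for independent children; it does not hold in the middle of the stated range, nor for a three-school sample at small intraclass correlations

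*Protocol*

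**What the plan says.** Protocol section 8.2 (Infection) sets the aim: "We will test the hypothesis that estimates of PR will be similar using the two methodologies". The comparison is to be made for each biannual survey. The power statement takes 300 children per method in each survey as its sample size. Its claim reads: "we will have 80% power (one-sided significance level of 0.05) to reject the alternative hypothesis that there is a difference in estimates of PR". The margin attached to this claim is 10 points in absolute terms, and community PR may lie anywhere between 20% and 80%. The same paragraph says that systematic bias of the school method will be explored in both directions, upward and downward.

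The school sample is described as "300 children (3 schools x 100 children per school"). The community sample is 200 households at 1.5 children each. Section 6.1 says that the three schools are drawn at random from the primary schools of the sub-county and redrawn for each survey, so a school can appear more than once. The power statement mentions no ICC, design effect or other allowance for clustering. The named test is McNemar's test for paired proportions.

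**The concern.** Two features of the plan do not fit the power figure.

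- **Direction.** The margin is an absolute difference, so agreement within 10 points means excluding a difference of 10 points or more on both sides. A single one-sided test at 0.05 excludes only one side.
- **Clustering.** The 300 school children come from three schools. Pupils of one school tend to share local exposure, so they carry less information than 300 independent children. With 100 pupils per school, even a small ICC matters.

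The figure is the only quantitative support for the parasitemia part of objective 2, the validation of school surveys against community surveys. If it is too high, a non-significant difference in one survey may be read as well-powered evidence of agreement. Equally, the chance draw of three schools may be read as failure of the school method.

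**Working it through.** **Inputs from Protocol section 8.2.** n = 300 per method per survey; one-sided alpha 0.05 (z = 1.645); margin 0.10; PR p from 0.20 to 0.80; school sample 3 × 100. True difference taken as zero.

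**Step 1: reproduce the stated 80%.** SE = √(2p(1−p)/300). One-directional power = Φ(0.10/SE − 1.645). At p = 0.50, SE = √(0.50/300) = 0.0408 and power = Φ(2.449 − 1.645) = 79%. The same formula gives 80% at PR 40/60%, 85% at 30/70% and 92% at 20/80%. It needs 310 per method for 80% at PR 50%, close to the planned 300. The wording could also mean one-sided power to detect a 10-point difference; that gives 79.4% for 50% against 60%. Both readings are one-directional and unclustered.

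**Step 2: require both directions.** Two one-sided tests at 0.05: power = 2Φ(0.10/SE − 1.645) − 1.

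| PR | One direction | Both directions |
|---|---|---|
| 50% | 79% | 58% |
| 40/60% | 80% | 61% |
| 30/70% | 85% | 70% |
| 20/80% | 92% | 84% |

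A simulation at PR 50% gave 56%. Reaching 80% in both directions at PR 50% would take about 429 per method; at PR 20/80% it takes 275, so the planned 300 suffices there if children are independent.

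**Step 3: add school clustering.** School design effect DE = 1 + 99 × ICC; SE = √(p(1−p)/300 × (DE + 1)). The ICC values are assumptions, since the protocol gives none. Household clustering is ignored.

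| ICC | DE | Effective school n | Both directions, PR 50% | Both directions, PR 20/80% | One direction, PR 50% |
|---|---|---|---|---|---|
| 0.005 | 1.50 | 201 | 42% | 73% | 71% |
| 0.01 | 1.99 | 151 | 28% | 61% | 64% |
| 0.02 | 2.98 | 101 | 7% | 40% | 54% |
| 0.05 | 5.95 | 50 | 0% | 0% | 37% |

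Example, ICC 0.01 at PR 50%: SE = √(0.25/300 × 2.99) = 0.0499; 2Φ(2.003 − 1.645) − 1 = 28%.

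**Step 4: where power reaches zero.** In this approximation it does so when 1.645 × SE is at least 0.10, that is DE + 1 ≥ 300 × (0.10/1.645)² / (p(1−p)). At PR 50% the limit is DE = 3.44, ICC about 0.025. At PR 30/70% it is ICC about 0.033, and at PR 20/80% about 0.050.

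**Step 5: what the approximation leaves out.** Three clusters leave few degrees of freedom for the between-school variance, which lowers these figures. A finite-population correction raises them, but the number of schools per sub-county is not given. For illustration, with S schools DE becomes 1 − ICC + 100 × ICC × (1 − 3/S). At ICC 0.02 and PR 50%, power is then 19% if S = 10 and 28% if S = 6, against 7% without the correction.

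**The case against.** The strongest counter-arguments are these.

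- **The clustered loss rests on an assumed ICC.** This stands. A reader might infer that once clustering is counted a single survey has no power, or cannot show agreement even if the two methods are identical. The documents do not support that: it is true only above an ICC of about 0.025 at PR 50%, or 0.050 at PR 20/80%, and no ICC is given.
- **PR 50% is the worst case.** This also stands. Without clustering, the two-directional power at 20/80% is 84%, so the direction problem affects only the middle of the range. Table 1 reports older parasite rates (1999, ages 2–9) of 15%, 43% and 91%. By the step 3 formula at ICC 0.02 these give 57%, 9% and 84%, so the effect would differ greatly by site.
- **The conclusion does not rest on this test alone.** Section 8.2 explores bias whatever the test shows, adds regression and prospective validation, and rejects a school method only if bias correction is also unreliable. This limits the damage, but it does not make the stated 80% correct.
- **Pooling would restore the power.** It would raise it, but a reader should not infer that pooling settles the matter. Schools may be drawn more than once, so site-surveys are not fully independent, and opposite biases at different sites could cancel in a pooled average.

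Leaving details to a statistical analysis plan is no answer, because the protocol states a specific figure and that figure does not follow from its own design.

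**Conclusion.** The point holds in conditional form. The 80% is correct arithmetic for a narrower question: one direction, 300 independent children per method. For similarity in both directions it is wrong from PR 30% to 70% even without clustering, with power of 58% to 70%. This part needs no outside figure, only a true difference of zero and the normal approximation.

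The three-school design lowers power further by an amount the protocol does not allow anyone to fix. At an assumed ICC of 0.01, two-directional power is about 28% at PR 50% and 61% at PR 20/80%. The one-directional reading also falls to 64% at PR 50%, so choosing that reading does not rescue the claim. What can be concluded is that a single site-survey may well fall short of 80%, not that it has no power.

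**What to change.** Rewrite the power paragraph in Protocol section 8.2, with the sample size unchanged:

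1. State power for two one-sided tests at 0.05 with a margin of ±10 points, by PR across the 20–80% range.
2. Apply a school design effect of 1 + 99 × ICC over a stated ICC range. Declare any household design effect as an assumption. If the number of primary schools per sub-county is known from the enumeration, give it and apply the finite-population correction.
3. Say that a single site-survey may not reach 80% power.
4. Name a comparison for independent, clustered samples that matches this power statement, in place of the paired McNemar test; the school and community samples are drawn separately.
5. If power is also claimed for a comparison pooled over site-surveys, allow for schools drawn more than once, describe the result as average agreement only, and report the site-specific differences beside it.

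The cost is one rewritten paragraph, a change to the named test and a less favourable per-survey figure. No extra children or schools are required.

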# 4.0 STUDY METHODS

## 4.1 Overall study design

We propose to conduct cross-sectional surveys in communities and primary schools twice a year for at least 2 years in the 3 different sites. The surveys will be timed to correspond to the high and low malaria transmission seasons, when possible. In the community surveys, 200 households will be recruited from a list randomly generated from a census database at each site. The community surveys will consist of three components: (1) a household survey targeting heads of households, (2) a women’s survey targeting all women of child-bearing age (15-49 years), and (3) clinical surveys of all children under fifteen years of age, and of one household member within the age category 15-24 years, 25-34 years, 35-44 years, 45-54 years, and > 55 years. The clinical surveys will include a fingerprick blood sample for measurement of hemoglobin, thick and thin blood smear, rapid diagnostic test (RDT) for malaria, and filter paper blood sample. The school surveys will be conducted in 3 randomly selected primary schools per site. A total of 100 randomly selected children will be recruited in each school. The school surveys will include only the clinical assessments including measurement of temperature, and a fingerprick blood sample for measurement of hemoglobin, thick and thin blood smear, RDT for malaria, and filter paper blood sample.

##

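### The ecological logistic regression that predicts community from school parasite rates leaves out the school estimate's own sampling error, so in its ordinary form its standard errors and intervals are too small

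*Protocol*

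**What the plan says.** In Protocol section 8.2 (Infection), the school PR in each survey is based on "300 children (3 schools x 100 children per school") and the community PR on "300 children (200 households x 1.5 children per household"). Under section 6.1 the three schools are drawn afresh for every survey. Section 4.1 sets the surveys at "twice a year for at least 2 years in the 3 different sites", which gives at least 2 x 2 x 3 = 12 site-surveys.

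Bias between the two methods is to be explored whatever the significance test shows, and the tool is named: "Ecological logistic regression models will be used to predict the result of the gold standard method using data from the streamlined method". Its stated purpose includes correcting the school result for bias. The next sentence adds a check: "Final models will then be prospectively validated in independent test sets to insure their accuracy". The closing paragraph of section 8.2 rejects the school method if it does not approximate the community result and "attempts at correcting systematic bias are not reliable (e.g. unable to consistently predict estimates using the gold standard method").

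For infection, the only error structure that section 8.2 states is the binomial confidence interval. For mortality, the same section gives a variance for each of the two methods (delta method and bootstrap).

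**The concern.** The information on school-versus-community bias lies in the site-survey pair: one school PR set against one community PR. An ordinary logistic regression of the community result on the school PR conditions on the predictor and gives the outcome binomial variance only. The disagreement actually seen between the two figures also contains the sampling error of the school PR, and that error has no place in the model. With 300 children on each side it is as large as the community error before any clustering, and larger if pupils within a school are alike.

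Two results would mislead. A test for systematic bias would reject too often when the methods agree, which invites a correction to school estimates that need none. And the interval around a predicted community PR would look much tighter than the prediction deserves. Robust errors for households on the community side would not help, because the missing error is on the school side.

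**Working it through.** **The plan's own figure.** Section 8.2 gives no figure for the regression. Its 80% power claim (300 children per method, 10-point difference, one-sided 0.05, PR 20-80%) reproduces as a comparison of two independent binomial proportions. In the worst case (50% against 40% or 60%) power is 79.4%, and 305 per method would give 80%. It reproduces only if children count as independent on both sides.

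**Inputs.** From the protocol: 300 pupils in 3 schools of 100; about 300 community children; 12 site-surveys. Assumed: true PRs of 20/50/80% at the three sites (within the protocol's range), no true bias, and school ICCs of 0 to 0.10. The protocol gives no ICC.

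**False findings of average bias.** Take logit(school PR) as offset and test whether the intercept is 0. Let v be the binomial variance of a logit PR from 300 children.
- Model variance per pair: v
- True variance per pair: v + v x D, with school design effect D = 1 + (100 - 1) x ICC
- Ratio R = 1 + D (the small household effect is ignored)
- Actual rejection rate = 2 x [1 - Phi(1.96/sqrt(R))]

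At ICC 0, R = 2 and 1.96/1.414 = 1.386, giving 16.6%. At ICC 0.05, D = 5.95 and R = 6.95; 1.96/2.636 = 0.743, giving 46%.

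**Coverage at a new survey.** The simulated 95% interval for the fitted community PR has a half-width of about 2 points, so its model standard error is 2/1.96 = 1.02 points. The true variance of the fit is about R x 1.02². The new survey's school PR adds its own error. Averaged over PRs of 20, 50 and 80%, the binomial variance is (5.33 + 8.33 + 5.33)/3 = 6.33 squared points, multiplied by D. At ICC 0 the total is 2.08 + 6.33 = 8.41, SD 2.90, and P(|Z| < 2/2.90) = 51%.

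**Formula against simulation** (ordinary binomial fit, no true bias, PR 20/50/80%, 12 site-surveys; ranges are over runs with household ICCs from 0 to 0.2; Monte Carlo error up to about 4 points):

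| School ICC | D | R | Rejection, formula | Rejection, simulated | Coverage, formula | Coverage, simulated |
|---|---|---|---|---|---|---|
| 0 | 1 | 2 | 17% | 16-19% | 51% | 47-53% |
| 0.01 | 1.99 | 2.99 | 26% | 25% | 39% | 39% |
| 0.02 | 2.98 | 3.98 | 33% | 33-35% | 32% | 33% |
| 0.05 | 5.95 | 6.95 | 46% | 46-47% | 23% | 21-26% |
| 0.10 | 10.9 | 11.9 | 57% | 53-64% | 18% | 19% |

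If binomial noise is added so that the interval targets the next *observed* community PR, as a validation exercise would, coverage is 80-83% at ICC 0, 66% at 0.02, 57% at 0.05 and 48% at 0.10.

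**Remedies, same no-bias setting, school ICC 0 to 0.10.** A one-sample t-test on the 12 logit differences rejects 4-6%. The same logistic regression with Pearson dispersion scaling and t quantiles rejects 2.5-6% and covers the next observed community PR 94-96% of the time. With survey-level robust errors and t quantiles it rejects 6-7%.

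**Slope.** The mean fitted slope (true value 1) is 0.99, 0.97, 0.93 and 0.88 at ICC 0, 0.02, 0.05 and 0.10. If the site PRs lie close together (40/50/60%), it is 0.94, 0.83, 0.71 and 0.57. After dispersion scaling, false slope findings at PR 20/50/80% are 4-8% at ICC 0 to 0.02, but still 14% at 0.05 and 20% at 0.10.

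**The case against.** The protocol gives this model one sentence. It does not say that the school PR is exact, that children are independent replicates, or which variance estimator will be used. The word ecological points to the survey as the unit, and an analysis plan that is not shown could supply the variance. This part stands: the fault belongs to the ordinary form of the named model, read beside a section that states only binomial error for infection. It is not something the protocol declares. It is still more than missing detail, because the model is fixed and followed as written it gives wrong error bars.

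A reader might infer that the decision on school surveys will go wrong. The documents do not support that. The rule requires both failure to approximate the community result and unreliable correction, and it cites no p-value or interval. The model is also to be validated prospectively, which could expose over-precise predictions. No validation criterion is given, however, and validation judged by the ordinary intervals could fail a sound school method.

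A reader might also take the flattened slope as a main defect. It is minor over PR 20-80% at low ICC. For prediction from future school surveys of the same design, regression on the observed school PR is appropriate. With site PRs of 40/50/60% and ICC 0.05, the fitted model predicted the true PR better than the raw school PR did (root mean squared error 6.0 against 6.9 points). With PRs of 20/50/80% it was slightly worse (6.6 against 6.0).

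Nor must the model be discarded: survey-level variance repairs the bias test and the prediction coverage.

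**Conclusion.** The point holds as one about understated variance. With no true bias, the ordinary fit turns a nominal 5% test of average bias into one that rejects about 17% of the time at school ICC 0, a figure that needs no assumed clustering. It rejects about 35% to 56% at ICCs of 0.02 to 0.10. The nominal 95% interval for community PR at a new survey covers about 50% at ICC 0, falling to about 19% at 0.10. Every figure above ICC 0 rests on an assumed ICC, and all rest on the ordinary binomial fit.

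This is a raised rate of false bias findings, not a certainty of finding bias, and it overstates the precision of predictions. A wrong decision on school surveys is a possible consequence that the documents do not establish. The change should be made, because it is cheap and the bias analysis depends on it.

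**What to change.** In section 8.2, make the site-survey pair the unit for assessing bias, in one of two ways:
- analyse the paired differences logit(school PR) minus logit(community PR), with a t-based interval over pairs and limits of agreement; or
- keep the ecological logistic regression and add survey-level extra-binomial variance (dispersion scaling or survey-level robust errors) with t quantiles.

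State that consistent prediction and the prospective validation will both be judged by a prediction interval for a new survey that includes this between-survey variance. Add an errors-in-variables or bivariate model only if the slope itself is to be interpreted, since dispersion scaling does not remove its attenuation.

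The cost is wording and a little more analysis, with wider intervals for the bias and the predicted community PR. No extra children, schools or surveys are needed.
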